## 16.2 Definition of study outcomes

|                         |                                                                                                                                                             |                                                                                                                 |                                                                                                         |                           |                                                                                                            |                                                                                                          |                                 |                       |
|-------------------------|-------------------------------------------------------------------------------------------------------------------------------------------------------------|-----------------------------------------------------------------------------------------------------------------|---------------------------------------------------------------------------------------------------------|---------------------------|------------------------------------------------------------------------------------------------------------|----------------------------------------------------------------------------------------------------------|---------------------------------|-----------------------|
| Objective response (OR) | Confirmed complete response (CR) or partial response (PR), defined according to RECIST criteria, persisting $\geq 4$ weeks after the initial documentation. | Confirmed objective responses plus confirmed stable disease (SD $\geq 24$ weeks), according to RECIST criteria. | Time from the first dose of study medication to the first documentation of an objective tumor response. | Duration of response (DR) | Time from the first dose of study medication to the first documentation of an objective tumor progression. | TTP will be censored at the date of death for patients who have not had objective disease progression.   | Progression-free survival (PFS) | Overall survival (OS) |
|                         |                                                                                                                                                             |                                                                                                                 | Time from the first time of progression or death as a result of any cause.                              |                           | Time from the first dose of study medication to the first documentation of an objective tumor progression. | Time from study enrollment to time of death as a result of any cause.                                    |                                 |                       |
|                         |                                                                                                                                                             |                                                                                                                 |                                                                                                         |                           |                                                                                                            | Survival time will be censored at the date of the last follow-up visit for patients who are still alive. |                                 |                       |

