## 6. STUDY DESIGN

This will be a non-randomized, open label, phase I/II, multi-centre study of sorafenib in combination with fixed doses of vinorelbine as first-line treatment for women with metastatic breast cancer.

In the Phase I of the study, 6-12 patients will be recruited in a single center (Jewish General Hospital, Montreal).

In the Phase II part, 21-24 more patients will be recruited and treated in six different centers in Quebec.

The first part of the study will test increasing doses of sorafenib, combined with regular administration of vinorelbine at fixed therapeutic doses (30 mg per square meter on days 1 and 8 of 21-day cycles).

Dose escalations will be made in subsequent cohorts of patients, up to the recommended dose for sorafenib monotherapy. Sorafenib doses will be: 200 mg bid (cohort I) and 400 mg bid (cohort 2).

In the second part of the trial, the cohort of patients treated at the recommended dose will be expanded, up to a total of 27 patients treated with this schedule of the combination regimen (see Section 16.2).

Six patients treated at the recommended dose will be assessed for pharmacokinetic analysis.

Clinical follow-up, including physical examination, laboratory testing and evaluation of adverse event will be performed on day 1 and 8 of each cycle.

Patients will have appropriate radiological imaging to document baseline disease within 4 weeks prior to study entry. Radiological imaging will be repeated regularly after every two cycles, until disease progression or unacceptable toxicity, up to 8 cycles (or after at least 4 cycles after achievement of the best response obtained).

Those patients whose disease has not progressed during the combination treatment, will continue receiving sorafenib alone at the dose of 400 mg bid and will be monitored every 42 days, with clinical and radiological follow-up.

All patients will be followed for a minimum of 2 years for survival and residual toxicity.

Safety will be assessed by examination of adverse events, clinical laboratory data, and vital signs. Adverse events, use of growth factors, and changes in laboratory parameters will be summarized and tabulated. Objective response (CR, PR, SD, and PD) will be summarized and tabulated. Time to response, duration of response, time to progression, and survival will be calculated. Kaplan-Meier estimates and curves will be used to present these time-to-event data.

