## 10.2 Monitoring of patients treated with combination therapy

During administration of sorafenib and vinorelbine, in both study phases, patients will be routinely assessed for adverse events and cell blood count on days 1 and 8 of every cycle.

A complete biochemical blood analysis will be routinely performed at day 1 of each cycle.

Blood samples will be collected on the same day of therapy administration, or, in case of necessity, within the preceding 24 hours.

Physical examination, laboratory testing and evaluation of adverse event will be performed more often, if clinically indicated.

Only for patients treated during the phase I (dose escalation) part of the study, additional blood samples will be collected for cell blood count on day 15 of the first two cycles and for hepatic function markers on day 8 and 15 of the first two cycles. The utility of maintaining these additional tests for patients treated in the phase II cohort will be discussed by the investigators after completion of the phase I.

Radiological imaging will be repeated regularly every 6 weeks (two cycles), unless all measurable disease is assessable by physical exam.

Assessment of tumor response will be performed as long as the patient remains on study, or until disease progression for patients removed from the study for other reasons. Patients who achieve complete or partial response will be re-evaluated at least 4 weeks later to confirm the initial observation of response.

A cardiac re-evaluation through 12-lead EKG plus echocardiogram or MUGA scan will be repeated every 12 weeks (4 cycles), or more often if clinically indicated.

Patients receiving sorafenib monotherapy, after documented disease control, will be assessed for adverse events, cell blood count and biochemical blood analysis on day 1 of 21-day cycles for the first 8 cycles of sorafenib monotherapy, and every 2 cycles (42 days) thereafter, until patient's removal from the study. Physical examination, laboratory testing and evaluation of adverse events will be performed more often, if clinically indicated.

Chest X-ray, bone scan, abdomen ultrasound will be repeated if clinically indicated or, for patients in study more than 12 months, approximately once a year.

All patients will be followed for a minimum of two years for survival.

schematic layout of procedures planned for regular assessment of patients on study.

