### 14. DISCONTINUATION OF THERAPY AND WITHDRAWAL FROM STUDY

A patient will stop receiving the study treatment and will be withdrawn from the study when any of the criteria is met:

- Progression of disease based on physical examination or radiological

- Patient's inability to tolerate therapy despite dose reduction. This includes allergic reactions not controlled with slower infusions and routine pre-medications.
  - Patient experiencing an adverse event that would mandate a dose reduction below 200 mg qd for sorafenib, or below 20 mg/m^2 for vinorelbine.
  - Withdrawal of informed consent.
  - Patient evaluated as non-compliant by the investigator.
  - Need of new anticancer treatments. Patient requiring palliative radiation therapy should have study drugs withheld during the course of radiation therapy and until recovery (at least 15 days after radiation). Such patients may be retreated with study drugs, provided that the metastases do not represent progression of disease and there is no evidence of radiation recall reaction.
  - Patient with clinical signs or laboratory test results consistent with pregnancy. The pregnancy will be followed up via the Pregnancy Monitoring Form.
- The investigator can discontinue the patient at any time, at his/her discretion.

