#### **16.5 Analysis of event-free times**

The efficacy analysis will include Kaplan-Meier curves for TTP, PFS and OS, including quartiles for each variable. The 80% confidence interval of the median event-free time will be estimated using the standard error derived by Greenwood's formula. Covariates will not be included in the calculation of median survival time.

Kaplan-Meier analysis (Kaplan and Meier 1958) will be done using PROC LIFETEST in Statistical Application Software (SAS) (SAS Institute, Inc. 1989), or other equivalent statistical package. Other analyses will be done as necessary.

Kaplan-Meier curves and quartiles will illustrate also time to response and duration of response, if a sufficient number of responders is observed.

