## Confirmation

In some circumstances it may be difficult to distinguish residual disease from normal tissue. When the evaluation of complete response depends on this determination, it is recommended that the residual lesion be investigated (fine needle aspirate/biopsy) to confirm the complete response status.

Patients with a global deterioration of health status requiring discontinuation of treatment without objective evidence of disease progression at that time should be classified as having "symptomatic deterioration". Every effort should be made to document the objective progression even after discontinuation of treatment.

|                |                        |           |                    |             |                  |
|----------------|------------------------|-----------|--------------------|-------------|------------------|
| Target lesions | CR                     | CR        | Non-Target lesions | New Lesions | Overall response |
| CR             | CR                     | CR        | CR                 | No          | CR               |
| CR             | Incomplete response/SD | No        | PR                 | No          | PR               |
| PR             | Non-PD                 | No        | PR                 | No          | PR               |
| SD             | Non-PD                 | No        | SD                 | No          | SD               |
| PD             | Any                    | Yes or No | PD                 | Yes or No   | PD               |
| Any            | Any                    | Yes       | PD                 | Yes         | PD               |

The best overall response is the best response recorded from the start of the treatment until disease progression/recurrence (taking as reference for PD the smallest measurements recorded since the treatment started). In general, the patient's best response assignment will depend on the achievement of both measurement and confirmation criteria.

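### Section 16.2 censors TTP at death instead of at the last tumour assessment, which can raise the TTP curve if some patients stop assessment early

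*Protocol*

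**What the plan says.** The outcome table in section 16.2 is damaged in the extracted text, but two statements are legible. One is an event definition that fits TTP: "Time from the first dose of study medication to the first documentation of an objective tumor progression". The other names TTP and fixes its censoring: "TTP will be censored at the date of death for patients who have not had objective disease progression". Section 16.5 commits to reporting it: "The efficacy analysis will include Kaplan-Meier curves for TTP, PFS and OS, including quartiles for each variable".

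The assessment schedule comes from several places:

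- Section 10.2, combination therapy: "Radiological imaging will be repeated regularly every 6 weeks (two cycles), unless all measurable disease is assessable by physical exam". The same section continues response assessment while the patient is on study, "or until disease progression for patients removed from the study for other reasons".
- Section 6, sorafenib alone: patients "will be monitored every 42 days, with clinical and radiological follow-up".
- Section 6, combination therapy: imaging runs until progression or unacceptable toxicity, which is narrower than section 10.2.
- Sections 6 and 10.2: survival is followed for at least two years.

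Patients can leave without progression. Section 14 opens with "A patient will stop receiving the study treatment and will be withdrawn from the study when any of the criteria is met" and lists intolerance, consent withdrawal, non-compliance and new anticancer treatment. Appendix E (Confirmation) recognises "Patients with a global deterioration of health status requiring discontinuation of treatment without objective evidence of disease progression at that time", and then asks that every effort be made to document progression after treatment stops.

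**The concern.** Censoring deaths is inherent in TTP. The difficulty is the date. After the last assessment a patient cannot contribute an event, yet the rule keeps her in the risk set until she dies. Deaths are followed for at least two years, while scans may end sooner.

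For example, take a patient who has stable disease at week 12, stops for general deterioration, has no further scan and dies at month 14. She counts as 14 months free of progression when about 3 were observed. If there are several such patients, the quartiles promised in section 16.5 read too long. The trial has one arm, so the error cannot cancel against a control group.

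**Working it through.** The protocol states no TTP figure, so there is nothing to reproduce.

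**Direction.** The Kaplan-Meier estimate is S(t) = product of (1 − d/n) over event times up to t. Moving a censoring date from last assessment to death leaves every d unchanged and leaves every n unchanged or larger. Each factor is therefore unchanged or larger, and no quantile can fall.

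**Worked example, n = 27** (the planned number, section 16.1). Assumptions: three patients have their last scan at month 3 and die at month 15 without documented progression. The other 24 progress at t_j = −ln(1 − (j − 0.5)/24) × 6/ln 2, which is exponential with median 6 months. The 6 months is the single-agent time to treatment failure in section 2. That is a different endpoint and serves only as a scale.

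*Censored at last assessment.* Seven progressions precede month 3, so S = 20/27. Three patients leave and 17 remain at risk.
- Median: S = 20/27 × 11/17 = 0.479 at the 13th progression; t = 6.4 months.
- Upper quartile: S = 20/27 × 5/17 = 0.218 at the 19th; t = 12.8 months.

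*Censored at death.* All 27 stay in the denominator until month 15.
- Median: S = 13/27 = 0.481 at the 14th progression; t = 7.2 months.
- Upper quartile: S = 7/27 = 0.259 by month 15. Three leave and 4 remain; the 21st progression gives 7/27 × 3/4 = 0.194; t = 16.7 months.

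The same calculation for other numbers of such patients, as median / upper quartile in months. The middle column puts death 6 weeks (1.4 months) after the last scan, at 3 + 1.4 = 4.4 months.

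| Patients | Last assessment | Death 6 weeks later | Death at month 15 |
|---|---|---|---|
| 1 | 6.3 / 12.0 | 6.3 / 12.0 | 6.3 / 13.4 |
| 3 | 6.4 / 12.8 | 6.4 / 12.8 | 7.2 / 16.7 |
| 5 | 6.4 / 12.0 | 7.3 / 13.7 | 8.2 / 15.9 |

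With a 6-week gap nothing moves until five patients are affected, and then the median moves by one ordered progression time.

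**Schedule kept.** This was simulated with scans every 42 days until progression or death and 24 months of follow-up. About 3.7% die without documented progression (12-month median survival after progression assumed), with a median gap of 1.0 month. Median (6.9) and upper quartile (13.8) are the same under both rules.

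**Early stopping at random.** 200,000 patients, median TTP 6 months, median survival after progression 12 months (assumed), cut-off 36 months. With 10/20/30% leaving assessment (assumed), the median reads 6.2/6.6/7.1 months against 6.0, and the upper quartile 13.2/15.3/20.7 against 12.0. These figures apply the rule only to patients who die. If leavers still alive at cut-off are also held in the risk set, the medians are about 6.3/6.8/7.5.

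**At trial size.** In 3,000 simulated trials of 27 with 15% stopping at random, the median was never lower under the protocol's rule. It was unchanged in 67% of trials, and the mean shift was +0.65 months.

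**What the fix leaves.** Suppose a share p leaves just before progression. Censoring at last assessment then gives a hazard of (1 − p) times the true one and a median of 6/(1 − p). For p = 0.20 that is 7.5 months, against 8.2 under censoring at death and a true 6.0. So (7.5 − 6.0)/(8.2 − 6.0) = 68% of the bias remains.

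**The case against.** The strongest reply is that the protocol already plans to close the gap. Section 10.2 continues assessment until progression after removal from study, section 6 keeps 42-day radiological follow-up on monotherapy, and Appendix E asks for every effort to document progression. A patient unscanned from week 12 to month 14 departs from the plan. This stands, and it makes the effect conditional. It does not remove it. Consent withdrawal and non-compliance can end scanning whatever section 10.2 asks, and section 6 words imaging more narrowly after unacceptable toxicity.

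A reader might infer that the reported TTP quartiles will be inflated by months. The documents do not support that, because they give no share of patients who stop assessment. At 10% stopping at random the median moves 0.2 months, whereas the 10th to 90th percentile sampling range of the median in trials of 27 is 4.2 to 8.6 months.

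A reader might also infer that TTP will be judged against historical vinorelbine data. No TTP benchmark, hypothesis or decision rule is stated. The only formal benchmark is the 43% response rate in section 16.1, and section 5.2 lists median PFS but not TTP.

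The fix is also only partial when patients leave because they are about to progress. That stands too.

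**Conclusion.** The rule is stated in the protocol and the censoring date is poorly chosen. The direction is certain: against last-assessment censoring, TTP is unchanged or longer. The size is conditional. It is negligible if 6-weekly assessment until progression is kept. Under the assumed 10 to 30% stopping at random, the median reads roughly 6.2 to 7.5 months instead of 6.0, and the upper quartile moves more. These figures rest on exponential times, an assumed 12-month median survival after progression and a 36-month cut-off. Shorter follow-up captures fewer of the deaths and reduces the shift.

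No error is inferred for living patients, whose TTP censoring rule is not visible in the damaged table. The matter is minor: TTP is supportive, and the response analysis, the sample size and PFS are untouched.

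**What to change.** Replace the sentence in section 16.2 with: *For patients who die without documented objective progression, TTP will be censored at the date of the last evaluable tumour assessment, or at the first dose if there is none.*

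Reconcile sections 6 and 10.2 on whether imaging continues after treatment stops for toxicity. Keep PFS, whose entry in section 16.2 refers to death from any cause, as the endpoint for interpretation, because informative censoring in TTP is reduced but not removed.

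The cost is one sentence and one reconciliation, with no new data for the censoring change. Reported TTP may be slightly shorter, with fewer patients at risk late in the curve.

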#### **5.2 Secondary Objectives**

To assess:

- toxicity and safety;
- median time to best response;
- median duration of response;
- median progression free survival;
- overall 2 year survival in women with metastatic breast cancer, when treated with

the combination of vinorelbine and sorafenib at optimal doses.

To assess pharmacokinetic steady state parameters and interaction between vinorelbine and sorafenib when administered together at optimal doses.

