**Questions to:**  
DSI [contact]

If the report is made via telephone, a written report must follow as soon as possible, which includes a full description of the event and any sequelae. SAEs that occur at any time after the inclusion of the subject in the study (defined as the time when the subject signs the informed consent) up to 30 days after the subject completed or discontinued the study must be reported.

The subject is considered to have completed the study either after the completion of the last visit or contact (eg, phone contact with the investigator), or after the last dose of study medication, whichever is later.

The date of discontinuation is when a subject and/or investigator determines that the subject can no longer comply with the requirements for any further study visits or evaluations (e.g. the subject is prematurely discontinued from the study).

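### Overall survival censors living patients at the last follow-up visit but counts deaths at any date, which can bias 2-year survival and median OS downward if some survivors are followed only by contact

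*Protocol*

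**What the plan says.** Section 16.2 defines OS as "Time from study enrollment to time of death as a result of any cause". The definition does not tie the event to a visit. For survivors the rule is "Survival time will be censored at the date of the last follow-up visit for patients who are still alive". The outcome table reads out of order in the text available, but the wording of that sentence places it with OS. No section uses a last-known-alive date.

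The follow-up that feeds this endpoint appears twice. Section 6 says "All patients will be followed for a minimum of 2 years for survival and residual toxicity", and section 10.2 says "All patients will be followed for a minimum of two years for survival". Neither says whether this is done by clinic visit or by contact, and the term follow-up visit is not defined.

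Four other places bear on how the rule would work:
- Section 5.2 lists "overall 2 year survival in women with metastatic breast cancer" among the secondary objectives.
- Section 14 withdraws a patient from the study at progression, among other reasons.
- Section 15.5, defining study completion, treats a visit and a contact as different things: "completion of the last visit or contact (eg, phone contact with the investigator".
- Section 15.6 goes on recording deaths for follow-up purposes more than 30 days after study completion.

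Section 16.5 analyses OS by Kaplan-Meier.

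**The concern.** Kaplan-Meier assumes that the time at which a patient is censored carries no information about her survival. The rule in 16.2 can break this. A death enters at its own date however it is learned, whereas a survivor is cut back to her last visit. Any follow-up beyond that visit is then kept only for those who die.

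Take two patients who both stop treatment at month 6 and have no clinic visit afterwards. One dies at month 20 and contributes 20 months and an event. The other is confirmed alive by telephone at month 30 and contributes 6 months.

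Dropping survivors from the later risk sets while keeping the deaths inflates the estimated hazard, so the error runs in one direction: survival is understated. This is a single-arm trial, so there is no concurrent control to share the error, and a reader would set the 2-year figure against outside results.

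**Working it through.** **The plan's own figure.** The protocol gives no figure for OS. Its only sizing is for response rate (43% against 63%, one-sided 0.10, 80% power, 27 patients). With n = [(z₀.₉₀√(p₀q₀) + z₀.₈₀√(p₁q₁)) / (p₁ − p₀)]², the result is n = 27.08, and the power at 27 is 79.9%. The sizing reproduces under the normal approximation and does not involve OS.

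**Inputs for OS.**
- Median OS 18 months and median time to treatment failure 6 months, both for single-agent vinorelbine, from Protocol section 2. The 6 months stands in for the time of the last visit. Using these figures for the combination is an assumption.
- Assumed, not in the protocol: exponential times; last visit independent of survival; vital status known at a cut-off spread uniformly over 24 to 36 or 24 to 42 months from enrolment; and p, the share of patients followed by contact only after treatment.

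**Formula.** Let S(t) = 0.5^(t/18) be true survival, V(t) = 0.5^(t/6) the probability that the last visit is later than t, and A the probability of being alive at the cut-off. For t up to 24 months every death is counted, so the deaths are right, but the risk set is short:

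- at risk under the written rule = S(t) − p · A · (1 − V(t))
- estimated survival = exp{ −∫₀²⁴ f(t) / [S(t) − p · A · (1 − V(t))] dt }, where f is the density of deaths

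A is the average of S over the cut-off window. With λ = ln 2 / 18 = 0.0385, the 24 to 36 month window gives A = (0.397 − 0.250) / (12 × 0.0385) = 0.318. The 24 to 42 month window gives A = 0.286.

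For example, at month 12 with p = 0.5 and the longer window, the true at-risk share is 0.630. Under the rule it is 0.630 − 0.5 × 0.286 × 0.75 = 0.523.

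**Results at 24 months (true value 39.7%, true median 18 months).**

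| Contact-only share p | 2-year OS, cut-off 24–36 | 2-year OS, cut-off 24–42 | Median OS, cut-off 24–36 |
|---|---|---|---|
| 0 (all seen up to the cut-off) | 39.7% | 39.7% | 18.0 mo |
| 0.25 | 35.9% | 36.3% | 16.8 mo |
| 0.50 | 31.4% | 32.3% | 15.6 mo |
| 1.00 | 18.2% | 21.5% | 13.7 mo |

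Simulation of Kaplan-Meier at N = 27 (4,000 runs, 18-month uniform accrual, at least 24 months of follow-up) agrees: 36.5%, 32.4% and 21.6% for p = 0.25, 0.5 and 1.

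**Sensitivity.**
- Visits continue, the last one up to 1.4, 3 or 6 months before the cut-off: 39.6%, 39.5% and 39.3%. The loss is about 0 to 0.6 points, with simulation noise of about 0.3 points.
- Last visit correlated with survival (0.5, assumed): 36.6%, 33.1% and 23.1% for p = 0.25, 0.5 and 1.
- Median OS of 24 months (true 2-year OS 50%): 46.1%, 41.6% and 26.9%.
- Every survivor seen at or after month 24: the risk sets up to month 24 are complete, so the 2-year estimate does not change.

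**The case against.** The strongest reply is that the protocol never says survivors are followed by telephone. Follow-up for residual toxicity as well as survival (section 6) is compatible with clinic visits, and the last follow-up visit could naturally mean the last encounter of that two-year follow-up. Some assessments also continue after treatment. Section 10.2 carries on tumour assessment until progression in patients removed for other reasons, and section 15.3 follows adverse events after withdrawal. Patients who do not progress stay on sorafenib with regular visits, so 6 months may be too early for their last visit. The visit-or-contact distinction in section 15.5 was written for reporting serious adverse events, not for OS. Finally, OS is secondary, has no test or decision rule, and has a standard error near √(0.4 × 0.6 / 27) = 9 points, so the quarter-share loss of 3 to 4 points is under half of one standard error.

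Most of this stands, and it limits the point. A reader might infer that 2-year survival in this trial is biased downward, or that it would be reported as 18%. The documents support neither. The first needs survivors who are followed by contact and whose last visit precedes month 24; the second needs every patient to be contact-only. A reader might also infer that no assessment takes place once treatment ends, and sections 10.2 and 15.3 show otherwise.

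The reply does not remove the asymmetry in 16.2. Progression leads to withdrawal, no survival visit schedule is shown after it, and the protocol uses visit and contact as separate words. Sampling error does not excuse an avoidable error of fixed direction.

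**Conclusion.** The point holds conditionally. The rule as written makes censoring depend on outcome whenever a survivor is known alive after her last visit, and its effect on OS can only be downward. Whether it matters here depends on a follow-up mode that the protocol leaves open. Under the stated assumptions the loss in 2-year OS runs from essentially nothing (visits continue to near the cut-off), through roughly 3 to 4 points (a quarter contact-only) and 7 to 8 points (half), to about 17 to 22 points if all are contact-only. Median OS falls from 18 months to about 16.8, 15.6 and 13.7 months in the same three contact-only cases. These figures illustrate the mechanism; they do not predict this trial's result. The response-rate analysis and the sample size of 27 are not touched. A correction is still worth making because the alternative rule is no worse in any of these scenarios and protects a named objective.

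**What to change.** In section 16.2, replace the censoring sentence with one to this effect: a patient not known to have died is censored at the last date on which she is known to be alive, whether from a visit, a telephone contact or a record check. Apply one common data cut-off to deaths and to censoring, so that neither is taken from a later period than the other. State in section 10.2 how survival status is obtained after withdrawal, and add a last-known-alive date to the follow-up form.

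The cost is one sentence in 16.2, a line in 10.2 and one field on a form. No extra visits or patients are needed, and the primary analysis does not change.
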